**FIGURE 5 F5:**
[figure not shown]
Graphical representation of participant’s *T*-scores distribution in the Mental Health sub-questionnaire, and comparison with US population. An independent samples *t*-test showed that the scores in the Mental Health index of all BBHI participants (*N* = 4206; mean = 49.8; *SD* = 6.9) do not differ significantly from reference scores of the general US population (values taken from PROMIS Global health scoring Manual: mean = 50; *SD* = 10; *t* = 1.7, *p* = 0.10).

In order to select participants for the second phase of the study we calculated their scores in this sub-scale, transformed in standardized *z*-score, analyzed the resulting distribution (**Figure 6**), and selected, stratifying for age and sex, 500 participants from each of the two extremes of the distribution (1,000 in total). These two extremes represent participants with best and worst perceived mental-health of the cohort. The rationale for these selection criteria is to afford us the greatest possible signal to detect differences in biological correlates of brain health by comparing those with the best and worst self-reported brain/mental health. Indeed lower scores in these measures have been associated in previous studies with a variety of conditions like pain behavior, pain interference, fatigue, anxiety, depression, physical functioning, satisfaction with participation in social roles, and satisfaction with participation in discretionary social activities (Rothrock et al., 2010).

**FIGURE 6 F6:**
[figure not shown]
Graphical representation of participant’s *z*-scores distribution in the Mental health sub-questionnaire. The red circles marks the two selection groups at the two extremes of the distribution.

#### Assessments

##### Medical and physical exam

Medical and physical examination procedures were approved by the institution review board of the Institut Guttmann. Upon singing informed consent the participants undergo a medical evaluation and screening. This exam gathers medical personal and family history, social history, educational history, review of systems, and includes a medical exam, a cardiopulmonary exercise test (CPET), an evaluation of gait and balance, and a dual task performance test (Manor et al., 2016, 2018). Biological samples, initially focusing on blood and stool, are collected for laboratory tests and the determinations of biomarkers. Further blood samples are stored for genetic and epigenetic determinations. Biochemical, proteomics and metabolomic profiling will be carried out in plasma samples.

##### Cognitive assessment

The neuropsychological assessment comprises both paper and pencil, and computerized tests, administered in two separate sessions.

Paper and pencil assessment consists of a battery of well-established neuropsychological tests, exploring the different cognitive functions, while the computerized cognitive assessment includes four task used in the Cognition, Brain, and Aging study (COBRA; Nevalainen et al., 2015) evaluating processing speed and working memory.

The paper and pencil neuropsychological assessments evaluate general/fluid intelligence (WAIS-IV Matrices, Weschler, 2008), premorbid intelligence (National Adult Reading Test; Nelson and Willison, 1991) vocabulary (semantic verbal fluency, Peña-Casanova, 2005), selective attention (Cancelation test WAIS-IV; Weschler, 2008), executive functions (Trial making test B, phonemic verbal fluency; Reitan and Wolfson, 1985; Peña-Casanova, 2005) and working memory (Digit backward, Letter number sequencing), episodic memory (RAVLT; Rey, 1958), processing speed (digit symbol substitution; Weschler, 2008), motor and visuo-motor speed (finger-tapping, TMT-A; Reitan and Wolfson, 1985; Shimoyama et al., 1990), visuo-spatial abilities (Block design; Weschler, 2008).

##### Magnetic Resonance Imaging

Magnetic Resonance Imaging (MRI) data acquisition is undertaken using a 3 Tesla Siemens PRISMA scanner and a 32-channel head coil.

The MRI session lasts approximately 1 h and includes accelerated multiband sequences adapted from the Human Connectome Project (D) and provided by the Center of Magnetic Resonance Research (CMRR) at the University of Minnesota. The protocol includes several high resolution structural T1-, T2-weighted and a FLAIR scans, which will allow us to quantify longitudinal changes in cortical and subcortical volume, myelination, white matter integrity and vascular disease.

High-resolution multishell diffusion-weighted MRI (1.5 mm × 1.5 mm × 1.5 mm, 100 directions) is obtained to further characterize tissue integrity in white matter, where the anisotropy of water diffusion is known to capture the geometry and state of myelin sheaths along axonal tracts, but also within the cortex.

High resolution resting state functional MRI (fMRI) (2 mm × 2 mm × 2 mm and TR = 0.8 s) is acquired to study lifespan longitudinal changes in both whole-brain functional networks and patterns of local cortico-cortical coupling.

A second fMRI scan is acquired during a working memory and memory encoding tasks. To this end, two subgroups are randomly selected out of our Phase-II sample, each assigned to one memory task to avoid overloading the MRI protocol.

Finally, an advanced high resolution pseudo-Continuous Arterial Spin Labeling (pCASL) sequence is acquired to identify small focal lesions and quantify cerebral blood flow (CBF) and arterial transit time (ATT) in cortical and subcortical structures.

The brain anatomical MRI’s are reviewed with a neuroradiologist in order to generate a first report that might identify actionable findings and offer some return of results to participants.

##### Electroencephalography (EEG)

Thirty two channel EEG is acquired using the Enobio 32-channel EEG cap from Neuroelectrics (Barcelona, Spain) during rest (eyes open and eyes closed) and during the performance of an auditory Oddball task and a Flanker task. These tasks are used to collect event-related potentials (ERPs) to assess the neurophysiological response to conflict resolution monitoring and signal detection. Some changes in ERPs’ components elicited by these tasks, e.g., the P300 in the Oddball tasks, have been found to relate with information processing and age-related cognitive decline (see van Dinteren et al., 2014 for a meta-analysis). In addition, further electrophysiological EEG substrates are collected and analyzed such as frequency analysis oscillatory power bands and coherence, an index of the synchrony between cortical regions.

Neuroelectrics Instrument Controller software is used for initial EEG analysis in order to generate a first report that might identify actionable findings and offer some return of results to participants.

##### Transcranical Magnetic Stimulation and EEG

Transcranial magnetic stimulation combined with EEG allows the characterization of cortical excitability and reactivity (Pascual-Leone et al., 2011; Shafi et al., 2014; Farzan et al., 2016). Single pulse and paired pulse TMS using a Medtronic MagPro X100 stimulator, combined with high density TMS compatible EEG system (BrainProducts Brain ActiChamp, Gilching, Germany), are applied over 5 stimulation sites: primary motor cortex (M1), left and right inferior parietal lobule, and left and right lateral dorsolateral prefrontal cortex. These target areas are defined based each individual’s brain MRI and targeted using frameless stereotaxy. The targeting of these latter regions is based on the fact that they comprise nodes of two brain networks highly sensitive to the effects of aging, namely the fronto-parietal and the default mode network (DMN, Andrews-Hanna et al., 2007; Sala-Llonch et al., 2015; Damoiseaux, 2017), which is also critically affected in early stages of AD (Sheline and Raichle, 2013). Motor evoked potentials (measured via electromyography at the hand muscle) from M1 stimulation and TMS-evoked potentials (TEPs) are recorded from non-motor regions.

##### Participants Feedback and Incidental Findings Report

Once finished the in-person assessment an initial review of results is done by expert personal and supervised by a physician in order to identify actionable and incidental findings. Additionally, a brief report is developed that is subsequently sent to the participant with an explanation of which tests were performed, the result, and a brief overview of the significance of each test. Participants are informed about the lack of clinical value of this report and that this assessment does not substitute any medical or clinical assessment planned or previously done. Incidental medical findings are evaluated by the designated physician and communicated to participants as soon as an abnormality is detected during the assessments. Expert staff will be consulted as needed to assist with the interpretation of the results and the recommendations for follow-up (e.g., radiologist, neurologist/neurosurgery specialist, cardiologist, sleep physician,…). If it is determined that the participant would benefit from medical follow-up, he or she will be instructed to contact their general practitioner who will be provided with a report of the relevant findings. If there is concern for the participant’s immediate health, they will be referred to emergency medical care as needed.

### Phase III: Randomized Control Trial of a Multi-Dimensional Lifestyle Intervention

The third phase of the study is aimed to start in 2019 and will consist of a 6-month multi-dimensional intervention, administered via an Information and Communication Technology (ICT)-based platform. Five hundred participants from the general cohort who did not participate in phase II will be invited to participate. Phase III will be a randomized-control trial (RCT) of a multidomain intervention of remotely supervised coach-led lifestyle habits. A control group will consist of participants who receive education regarding healthy lifestyles but no coaching. All participants will undergo the in-person evaluations described in phase II at baseline and following the 6-month intervention. All participants will be monitored using mobile technologies to assess adherence to the multi-dimensional intervention and capture relevant metrics of physical activity, diet, sleep, etc.

#### Multi-Dimensional Intervention: Rationale and Characteristics

The multi-dimensional intervention will include cognitive training, physical exercise, adherence to the Mediterranean diet, maintenance of social activities, healthy sleep habits, and participation in mindfulness sessions. Several recent reviews and meta-analyses have demonstrated the weaknesses and inconsistencies of single physical, nutritional, or cognitive interventions (Brasure et al., 2018; Butler et al., 2018a,b) for the promotion of cognitive fitness and brain health. Indeed, the multi-factorial etiology of neurodegenerative diseases may necessitate the use of multi-domain interventions (Mangialasche et al., 2012). Accordingly, the need to evaluate the effects of multi-dimensional interventions is present (Kivipelto et al., 2013; Vellas et al., 2014; Kulmala et al., 2018) and a number of recent studies have assessed their effects. The Finnish Geriatric Intervention Study to Prevent Cognitive Impairment and Disability (FINGER; Kivipelto et al., 2013; Kivipelto et al., 2018) explored the effects of a multi-dimensional intervention composed of cognitive training, physical exercise, diet and monitoring of cardiovascular risk factors in preventing cognitive decline in at risk people as measured by the Cardiovascular Risk Factors, Aging, and Incidence of Dementia (CAIDE) score. After a 2-year intervention results showed a small benefit of the intervention in global cognitive functioning (Ngandu et al., 2015; Rosenberg et al., 2018).

Following the same logic Vellas et al. (2014) assessed in the Multidomain Alzheimer Prevention Trial (MAPT) the efficacy of: (1) a single domain supplementation with omega-3 fatty acid; (2) a multi-dimensional intervention including nutritional counseling, physical exercise and cognitive stimulation; or (3) a combination of the two. Initial data showed no significant effects of any of the interventions on cognitive decline over 3 years (Andrieu et al., 2017). However, a secondary analysis of the data narrowed to high-risk people using similar criteria of the FINGER study (i.e., CAIDE ≥ 6) found benefit of the multi-domain intervention in some cognitive outcomes (Chhetri et al., 2018).

Two important lessons can be derived from these results. Firstly, they highlight the importance of early interventions to prevent cognitive decline. That is, as previously mentioned (see Introduction), changes in the brain begin decades prior to the onset of symptoms and consequently, lifestyle interventions may be necessary across the whole lifespan, long before these changes commence.

Second, a large number of sensitive baseline measures are fundamental to detect true effects of lifestyle interventions on cognitive decline and prevention of neurodegenerative diseases, and fully explain and understand the different age-related trajectories (Nilsson and Lövdén, 2018).

Phase III of the BBHI aims to fill these gaps in knowledge through a multi-domain lifestyle intervention, during mid-life with a large number of baseline and post-intervention metrics sensitive to differences in brain health. Prior to launching, this third phase of the BBHI will be registered in clinicaltrials.gov.

All the intervention will be ICT-based, designing and developing a solution consisting on two main parts: (1) a mobile application (the BBHI app) that participants will download; and (2) a web-based portal for coaches. The BBHI app will allow us to administer, coach and monitor the different domains of the intervention program. Users will have access to the different modules (addressing the defined 7 brain health pillars) and the web-based portal will allow coaches managing and tracking their performances in these different domains. This *ad hoc* ICT-based developed solution will allow us to have all monitored data stored in our Data Warehouse, structured and ready for analysis.

At the time of writing the exact details of the Phase III protocol are under discussion with the International Scientific Advisory Board Members of the study. Consequently, the exact protocols for each intervention will be guided by the most up to date literature on each topic at the time of the phase launch. Notwithstanding, there is consensus regarding the general lines of the intervention, which will include the following modalities;

*Cognitive training*, administered by the BBHI app, will be developed in-house based on previous successful intervention studies (Schmiedek et al., 2010; Schweizer et al., 2011; Wolinsky et al., 2011; Sandberg et al., 2014). It includes tasks that engage different cognitive domains as attention (e.g., visual search), speed of processing (e.g., perceptual speed task), set shifting (e.g., task switching), inhibition (e.g., Stroop task), working memory (e.g., dual n-back task), reasoning (e.g., sequencing task) and memory (visual span and recent probe task*).* As the majority of cognitive training studies we will use a multi-domain approach, that have often reported better effects over-time than single-domain cognitive training (Cheng et al., 2012; Lampit et al., 2014).

*Physical exercise*, monitored by the BBHI app and wrist-based heart rate technology. A recent systematic review has shed light on the optimal dosages for consistent exercise-mediated improvements in aging (Gomes-Osman et al., 2018). In line with this approach the exact frequency, intensity and type of our exercise intervention will be determined by the extant literature at the time of phase launch.

*Nutrition*, where participants will be asked to follow a typical Mediterranean diet (Lourida et al., 2013), and their adherence to this dietary prescription will be assessed periodically by a questionnaire (Schröder et al., 2010) administered via BBHI app.

*Healthy sleep habits*, which will be guided by recommendations from Global Council for Brain Health^4^ and monitored by the BBHI app.

Finally, participants will be asked to participate in group sessions directed to help them to focus on what is important for them and live a values oriented life, using technique that include meditation and mindfulness (Franquesa et al., 2017).

#### Coaching and Monitoring

Monitoring and control of participant adherence to a multi-dimensional intervention has been highlighted as a fundamental methodological issue faced in previous studies (Kivipelto et al., 2013; Vellas et al., 2014). Numerous recent studies evaluating health coaching programs stress the relevance of monitoring and coaching (Dejonghe et al., 2017) to increase participant motivation and adherence (Barbera et al., 2018). Nevertheless, there is still a research gap in regard to feasibility, scalability, and long-term effectiveness.

Although health coaching can be seen as an interpersonal process, where communication and relation between the coach and the user are central aspects, ICT-based solutions offer very interesting opportunities, in both measurement as well as intervention (Rutjes et al., 2017; Barbera et al., 2018). One of the main advantages of coaching programs supported by technology is the possibility of seamlessly measuring behavioral data, thanks to devices and wearables which provide objective data about performance. Thanks to the potential of large datasets to provide learning opportunities via the implementation of artificial intelligent processes, the prediction of the effectiveness of each intervention can be calculated.

In our proposal, each coach will be responsible for the individualization and follow-up of the multi-dimensional activity programs. This will be implemented remotely with the use of ICT technologies (Simkin-Silverman et al., 2011; Barbera et al., 2018) and based on the SMART Goals (Bovend’Eerdt et al., 2009), Reinforcement Theory of Motivation (Cameron and Pierce, 1994) and Social Comparison (Festinger, 1954) theories.

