#### Effects of Intervention in Phase III

A recent meta-analysis (Zhu et al., 2016) proposed that the estimated combined effect size of physical and cognitive interventions, presented as Cohen’s *d*, is 0.29. In our study, considering α = 0.05, a β = 10 and an annual drop-out of 5%, we will be able to detect in a pre-post repeated measure ANOVA on the different outcomes (e.g., Flanker effect) between two groups of 250 participants a small effect *d* = 0.17.

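### Phase III's stated test and detectable effect of d = 0.17 make no allowance for clustering by coach and session group in the intervention arm; if outcomes are correlated within coach, both are optimistic

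*Protocol article*

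**What the plan says.** The section introducing Phase III describes a "randomized-control trial (RCT) of a multidomain intervention of remotely supervised coach-led lifestyle habits". Under Coaching and Monitoring, "each coach will be responsible for the individualization and follow-up of the multi-dimensional activity programs". The list of intervention components under Multi-Dimensional Intervention: Rationale and Characteristics closes with a group element: "participants will be asked to participate in group sessions directed to help them to focus on what is important for them".

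The comparison arm differs in structure. The Abstract and the Phase III introduction say that controls are educated and advised about healthy habits but are not coached. That controls attend no group sessions is an inference from this; no sentence says so directly.

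The statistical basis is under Effects of Intervention in Phase III. The inputs are "considering α = 0.05, a β = 10 and an annual drop-out of 5" per cent, the test is a "pre-post repeated measure ANOVA on the different outcomes (e.g., Flanker effect) between two groups of 250 participants", and the result is "a small effect *d* = 0.17". Principal Statistical Analysis adds, in general terms, linear regression with covariates. Neither section mentions coach, session group, an ICC, a design effect, random effects or robust standard errors. The article does not give the number of coaches, their caseload, or the size and permanence of the session groups. It also says that the details of Phase III were not yet final.

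**The concern.** Participants who share a coach receive a programme shaped and followed up by the same person, and those who share a session group also influence one another. Their outcomes may therefore be more alike than those of participants under different coaches. In the control arm no such units are described. This is a partially nested design: individuals are randomised, but clusters form in one arm only.

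A two-group ANOVA on 250 per arm counts every participant as an independent unit. With positive within-coach correlation, the intervention-arm mean is less precise than that analysis assumes. Confidence intervals are then too narrow, false positives are more frequent than 5%, and the detectable effect is larger than stated. The article gives a reason to expect some correlation, since it treats the relation between coach and user as central to coaching, but it gives no value.

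**Working it through.** **Inputs from the article.** 250 per arm; alpha 0.05 (taken as two-sided); beta printed as 10, read as 10%, so power 90%; drop-out 5% a year, hence about 2.5% over six months and 250 × 0.975 ≈ 244 analysed per arm; stated d = 0.17.

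**Step 1: the stated figure.** With independent participants and a comparison of post-treatment values only, the detectable effect is (1.960 + 1.282) × √(2/n). This is 3.242 × √(2/250) = 0.290, or about 0.293 with n = 244. Reaching 0.17 requires a pre-post correlation ρ, which the article does not give. With 244 per arm:

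- change score, multiplier √(2(1 − ρ)): ρ ≈ 0.83
- baseline-adjusted analysis, multiplier √(1 − ρ²): ρ ≈ 0.815
- group-by-time F-test, f² = 3.242²(1 − ρ)/(2 × 488) and d = 2f: ρ ≈ 0.33

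So 0.17 cannot be confirmed. All three routes assume independent participants, and none needs a cluster term to arrive at 0.17.

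**Step 2: allowing for clusters in one arm.** With m participants per coach, the design effect in the intervention arm is DE = 1 + (m − 1) × ICC. The variance of the difference changes from proportional to 1 + 1 to proportional to DE + 1, so it is inflated by (DE + 1)/2 and the standard error by r = √((DE + 1)/2). The actual type I error of the naive test is 2 × (1 − Φ(1.96/r)), the detectable effect is 0.17 × r, and power at 0.17 is Φ(3.242/r − 1.96).

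**Assumptions, not in the article:** m = 10 to 25 and ICC = 0.02 to 0.05, the ICC being that of the quantity analysed (change or baseline-adjusted outcome).

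| m | ICC | DE | Variance ratio | r | Type I error, formula (simulated) | Detectable d | Power at 0.17 |
|---|---|---|---|---|---|---|---|
| 10 | 0.02 | 1.18 | 1.09 | 1.044 | 6.1% (6.2%) | 0.177 | 87% |
| 10 | 0.05 | 1.45 | 1.225 | 1.107 | 7.7% (7.3%) | 0.188 | 83% |
| 25 | 0.02 | 1.48 | 1.24 | 1.114 | 7.8% (7.8%) | 0.189 | 83% |
| 25 | 0.05 | 2.20 | 1.60 | 1.265 | 12.1% (11.4%) | 0.215 | 73% |

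The simulated values come from naive two-sample tests with 250 per arm.

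**Step 3: sensitivity.** With 5 to 25 coaches for 244 participants and ICC 0.01 to 0.10, the type I error runs from 5.5% (25 coaches, ICC 0.01) to 28.7% (5 coaches, ICC 0.10), and the detectable effect from 0.174 to 0.313. With ICC 0, DE = 1 and r = 1, so nothing changes (simulated type I error 5.1%).

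**The case against.** The strongest objection is that this is analysis-plan detail in a condensed article about an unfinished design. The ANOVA appears only as the basis of the detection limit, the analysis section is generic, and a coach term could still be added. A reader might infer that the trial will definitely ignore clustering and that its errors are certainly too small. The article supports neither inference. No sentence rules out a coach term, and the size of any error rests on inputs it does not give. What survives is that the article does state a test and a number, and both are built on independence.

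Second, the assumed ICCs may be high. On the scale of the raw outcome SD, an ICC of 0.05 means a between-coach SD of √0.05 = 0.22, which is 77% of the cited literature effect of 0.29. That is a lot for outcomes such as the Flanker effect under remote coaching. The point has weight, but the ICC applies to the quantity analysed. If 0.17 rests on a correlation of about 0.83, the SD of change is √(2 × 0.17) ≈ 0.58 of the raw SD, and the implied between-coach SD is 0.22 × 0.58 ≈ 0.13, or 45% of 0.29. If coaching has no effect on anyone, and coaches are assigned without regard to prognosis, the ICC is zero and the 5% level holds. The inflation applies when coach effects are real but average to nothing.

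Third, some tempting additions do not hold. Unequal variance between arms matters very little with equal arm sizes. Coaching is part of the programme being tested, so an effect carried by good coaches is not spurious in itself; whether conclusions should extend beyond these particular coaches is a choice of estimand. Coach and group identifiers may well be captured already, since a coaches' portal and a data warehouse are described.

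**Conclusion.** The point holds in conditional form. The article describes clustering by coach in the intervention arm only, and the one test and detectable effect it states for Phase III allow for none. For any positive ICC the direction is certain: standard errors too small, type I error above 5%, and d = 0.17 too favourable. The size is not known from the article. Under the assumed 10 to 25 participants per coach and ICC of 0.02 to 0.05, variance rises by 9% to 60%, the type I error is about 6% to 12%, and 0.17 becomes 0.177 to 0.215. With many coaches and a very small ICC the effect is slight.

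The coach structure alone carries the conclusion. Session groups may add to it, but their permanence is not stated and their absence among controls is inferred. A reader might also infer that the trial is underpowered for the cited effect of 0.29. If 0.17 is accepted, that follows in only the most extreme scenario examined (5 coaches, ICC 0.10). The false-positive rate is therefore the sturdier concern.

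**What to change.** Before Phase III starts:

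- Specify a partially nested mixed model, with a random effect for coach in the intervention arm only, one for session group if groups are fixed, and small-sample degrees of freedom because coaches may be few.
- Keep coach and session-group identifiers in the analysis data.
- State the expected number of coaches, the caseload and an assumed ICC, and restate the detectable d with the resulting design effect and the pre-post correlation it relies on.

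This takes a short paragraph and two data fields. The price is somewhat wider confidence intervals and a less favourable detectable effect. If the estimated coach variance is close to zero, the result will be close to that of the simpler analysis.
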